#### Economic analyses

The economic evaluation will comprise a cost-effectiveness and cost-utility analysis from the public sector perspective and a cost-benefit type analysis from the employer’s perspective (Objective 3). A cost-effectiveness and cost-utility analysis will compare costs and outcomes associated with the Intervention to those associated with the Control Group at three time-points. For the initial within study analysis, the outcome measures used will be (a) changes in mean steps per day; and (b) a within study measure of QALYs determined from EQ-5D. QALYs will be adjusted for any imbalances between groups at baseline [86]. Thus, the initial analysis will present an estimate of cost-effectiveness of the intervention in terms of the incremental costs associated with increasing physical activity and a cost-utility analysis in terms of incremental costs per QALY gained. The uncertainty surrounding the estimates of cost and effects for the Intervention and Control Group will be investigated through the use of bootstrapping [87]. In a sensitivity analysis we will compare subgroups and assess the uncertainty in their incremental cost-effectiveness ratios (ICERs) by plotting the associated cost-effectiveness acceptability curves. The longer term analysis will employ a decision model, populated with reference to the literature, to link short term study outcomes to longer term impacts on health and wellbeing. The model structure will be informed by a review of other models undertaken in this area, including the modelling work undertaken for NICE (2008) [88]. Data will be embodied in the model through the specification of probability distributions for each parameter, to reflect the uncertainty. Probabilistic sensitivity analysis will be undertaken, using Monte Carlo simulation, to investigate the uncertainty surrounding the longer term estimates of costs, effects and cost-effectiveness of the intervention.

From the public sector perspective, the analysis will involve firstly generating ICERs using healthcare utilisation data and EQ-5D data. Secondly, from the employer’s perspective, the effect of physical activity on absenteeism will be used to estimate potential cost savings to employers (absenteeism model); and thirdly, we will employ an algorithm to translate changes in EQ-5D into quantifiable changes in productivity (productivity model [89–91]). Individual EQ-5D scores at baseline, 6 and 18 months will also be converted into estimated levels of productivity using this algorithm and the total productivity gain over 6 and 18 months for each group will be calculated. To calculate the ICER, from an employer’s perspective, the additional costs will be divided by the additional gain in total employee productivity by the Intervention Group.

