#### Recruitment of participants

Recruitment methods will include email invitation to employees and posters placed around each workplace advertising the study. Emails and posters will include the website address and a web-link will be added to the organisations’ intranet sites (previously tested in our pilot study [27]). Potential participants will be able to access further information (including the Participant Information Sheet) and register their interest to participate on the study website.

Potential participants will be asked to complete a screening questionnaire via the study website or by telephone, to confirm their eligibility, based on the following inclusion criteria: based at recruited worksite at least 4 h/day (within core hours of 8 am-6 pm) on at least 3 days/week; current contract lasts for duration of the study (i.e.18 months) (to exclude temporary workers); access to internet at work; able to give informed consent; able to communicate in English; no self-reported recent history of myocardial infarction or stroke or physical limitations that would limit ability to participate in physical activity (assessed using the Physical Activity Readiness Questionnaire) [32].

All participants who meet the eligibility criteria and consent to participate will be contacted by a member of the research team by telephone or email to complete the baseline assessment. Following this, clusters of participants will be randomised to the Intervention or Control Group using computer generated random numbers. Clusters have been defined as the smallest organisational unit (e.g. a department or office/floor) within each participating workplace.

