### Statistical analysis

For the primary analysis, mean steps per day at 6 months will be the dependent variable. A random intercept will be fitted at the cluster level (all other variables will be fixed effects), with group, organisation (in categories), and baseline mean steps per day added to the model (Objective 1). The main focus for the analysis will be the estimated coefficient representing the difference in mean steps per day between the Intervention and Control Group, adjusted for baseline differences. The model will then be extended through the inclusion of interactions involving group and relevant covariates to test for any differential effects of the intervention (e.g. age, sex, SEP, time discounting function). In light of the multiple testing involved, these subgroup analyses will be cautiously reported as hypothesis generating rather than confirmatory.

The primary analysis will then be repeated using 18-month follow-up data to investigate the effectiveness of the intervention for behaviour change maintenance (Objective 2). These analyses will be repeated with secondary health and wellbeing outcomes, and work-related outcomes (Objective 4 and 5). Further, sensitivity analyses will assess the impact of missing data using Multiple Imputation by Chained Equations (MICE), testing first whether missingness-at-random is plausible [82].

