#### Mediation analyses

Mediation analyses of early behaviour change (uptake and initiation) (4 weeks) and behaviour change maintenance (6 months from start of intervention and 12 months from cessation of intervention) will be conducted (Objective 6). Methods for assessing and estimating the direct/indirect effects of intervention in the presence of multiple mediator models will be employed [83]. Bootstrap re-sampling strategies will be used to avoid multivariate normality assumptions in placing confidence limits on the estimates of the proportion of the total intervention effect that is mediated [84]. However, these analyses must be interpreted cautiously given the limitation that the mediation model is assumed to be correctly specified both in functional form and in that no variables are omitted which affect the relationships between independent and mediator or between mediator and dependent variables.

Briefly, social networks will be constructed from the work colleague nomination data at baseline, 6 and 18 months using UCINet 6.9 [85]. These data will be supplemented by objective, real-time proximity data collected throughout the 6 month intervention period. Individual-level network variables, for example, density and centrality measures, will be derived and included in mediation analyses. Further analyses investigating the structure, characteristics, function and evolution of workplace social networks on physical activity behaviour change will be undertaken as part of a NIHR Career Development Fellowship.

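### The cost-effectiveness analysis does not carry over the primary model's cluster level, and its step outcome is a change score rather than the trial's adjusted effect

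*Protocol article*

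**What the plan says.** All references are to the protocol article.

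- *Recruitment of participants* makes the group the unit of randomisation: "Clusters have been defined as the smallest organisational unit (e.g. a department or office/floor) within each participating workplace". *Randomisation* stratifies allocation by organisation.
- *Statistical analysis* gives the primary model: "A random intercept will be fitted at the cluster level", "with group, organisation (in categories), and baseline mean steps per day added to the model (Objective 1"). The coefficient for group is the trial's effect. The model is repeated at 18 months for Objective 2, and then: "These analyses will be repeated with secondary health and wellbeing outcomes, and work-related outcomes (Objective 4 and 5"). Objective 3, the economic evaluation, is not on that list.
- *Economic analyses* (Objective 3) says "the outcome measures used will be (a) changes in mean steps per day", with QALYs from EQ-5D as the second outcome. It states adjustment for baseline imbalance for QALYs and for nothing else. On uncertainty it says "The uncertainty surrounding the estimates of cost and effects for the Intervention and Control Group will be investigated through the use of bootstrapping", and it adds acceptability curves for subgroups. It names no resampling unit, cluster term or organisation term.
- *Update on study progress* gives an ICC of 0.029 and 330 per group for d = 0.40 (about 1600 steps) at 90% power. It says that the mean and variance of cluster size were used but does not give them.

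**The concern.** Two features of the primary analysis do not reappear in the economic section.

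The first is the cluster level. Costs and effects of people in the same department or floor may be correlated, and the incremental cost and incremental effect then vary more than independent individuals would suggest. A bootstrap reproduces that variation only if it resamples the randomised units. Otherwise the ICER intervals and acceptability curves look more certain than they are.

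The second is the step effect. The primary analysis estimates a difference at follow-up adjusted for baseline steps and organisation. The cost-per-step analysis uses change from baseline. These are different estimators, so the trial could report one step effect as its main result and divide costs by another. Cost-effectiveness is in the trial's title, so the denominator should be the effect that the trial reports.

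**Working it through.** **1. The plan's own figures.** 660/0.85 = 776.5, which agrees with the stated 776. Without clustering, d = 0.40 with 90% power and two-sided 5% (sidedness assumed) needs 2 × (1.960 + 1.282)² / 0.40² = 131.3, so 132 per group. The plan has 330. The implied design effect is 330/132 = 2.50. The 330 cannot be checked further because the cluster sizes are not given. With equal clusters, DE = 1 + (m − 1) × 0.029 = 2.50 gives m ≈ 53.

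**2. What individual resampling would do.** This step is conditional on two assumptions: that individuals are resampled, and that the ICC of 0.029 also applies to the economic outcomes. The true SE is √DE times the naive SE, and a nominal 95% interval covers 2Φ(1.96/√DE) − 1.

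| Case | DE | √DE | Interval too narrow by | Coverage |
|---|---|---|---|---|
| Equal clusters of 8 | 1.203 | 1.097 | 9% | 92.6% |
| Equal clusters of 20 | 1.551 | 1.245 | 20% | 88.4% |
| DE implied by 330 per group | 2.50 | 1.581 | 37% | 78.5% |

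The article gives no ICC for costs or QALYs. At ICC 0 nothing is lost. At ICC 0.01, coverage runs from 94.2% (m = 8) to 88.8% (m = 53). At ICC 0.05 it runs from 90.8% to 69.8%.

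**3. Change score against the adjusted difference.** Assume equal SDs at baseline and follow-up and a baseline to follow-up correlation ρ, which the article does not give.

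- Variance ratio, change score to ANCOVA: 2(1 − ρ)/(1 − ρ²). At ρ = 0.7 this is 0.60/0.51 = 1.18. At ρ = 0.5 it is 1.00/0.75 = 1.33.
- Difference between the two point estimates for a chance baseline imbalance B: (1 − ρ) × B in size. For B = 200 steps this is 60 to 100 steps (ρ = 0.7 to 0.5). For B = 400 it is 120 to 200 steps, or 7.5% to 12.5% of the 1600-step target.
- Scale of B: the implied SD is 1600/0.40 = 4000. The SE of a baseline difference with 330 per group is 4000 × √(2/330) = 311 steps without clustering and 311 × 1.581 = 492 with DE 2.50. Imbalances of 200 to 400 steps are therefore ordinary, although stratification by organisation may reduce them.
- With B = 0 the two estimates coincide in expectation.

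**The case against.** The strongest reply is that most of this is silence. *Economic analyses* does not say that individuals are resampled, and a cluster-level or two-stage bootstrap fits its sentence. The article is condensed, and a statistical or health economics analysis plan may name the unit. Steps, EQ-5D and absenteeism, which feed the economic models, each fall under the cluster model in *Statistical analysis*. Change in steps may be meant as an outcome and not as an estimator.

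Much of this stands, and it rules out stronger readings that a reader might infer:

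- That the plan discards clustering and its intervals are certain to be too narrow. The text supports only that the cluster level is not carried over.
- That baseline steps are ignored. A change score uses them, though not in the way the primary model does.
- That the change score is systematically wrong. It is unbiased over randomisation. It is less precise, and it departs from the primary result only when the arms differ at baseline by chance.
- That the bootstrap in *Mediation analyses* has the same fault. There too the unit is unstated, but that is only missing detail.

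Two things remain. First, the article does not leave all handling of correlation to another document. It assigns the cluster model by objective and omits Objective 3, and for the field experiment it specifies standard errors clustered on participant. Costs, derived QALYs and the joint cost-effect uncertainty are left without any stated cluster level. Second, the step outcome is a stated choice: change in steps, with baseline adjustment mentioned for QALYs alone.

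**Conclusion.** The point holds in a limited form. The economic section does not carry over the cluster structure, and its step outcome as written is not the baseline- and organisation-adjusted difference that the trial treats as its effect.

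The cost of the change score is 18% to 33% more variance, and a gap from the primary estimate of 60 to 200 steps for imbalances of 200 to 400. Both rest on assumed correlations of 0.7 to 0.5 and equal SDs.

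The clustering risk is conditional on individual resampling. Coverage would be about 93%, 88% or 78% for clusters of 8, clusters of 20, or a design effect of 2.5, if the steps ICC of 0.029 applies to the economic outcomes. The 78% rests on a design effect back-solved from the steps power calculation and should not be quoted as the expected result. Neither the cluster sizes nor the cost and QALY ICCs are known, and at an ICC of zero there is no loss.

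**What to change.** 1. In the cost-per-step analysis, use the adjusted difference in steps from the primary model as the incremental effect, and re-estimate it in each resample.
2. Base all ICER uncertainty and acceptability curves on a cluster-level or two-stage (cluster, then person) bootstrap within organisation and arm. Alternatively, use a bivariate multilevel model of cost and effect with a cluster random effect.
3. Choose between the two by the number of clusters, which the article does not give. At 330 per group, equal clusters of 8 mean about 41 per arm, but clusters of 53 mean about 6. Where an organisation has only one or two clusters in an arm, resampling within that stratum has little to work with, and the multilevel model is safer.

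The cost is a few sentences, somewhat more analysis code and, where clustering is present, wider intervals than individual resampling would give. No data collection or sample size changes.

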After the intervention (at 6 months), a random sample of 200 participants will participate in a behavioural economic field experiment aimed at eliciting individuals’ inter-temporal preferences and discount rates to identify participants who exhibit exponential discounting, hyperbolic discounting or quasi-hyperbolic discounting [80]. This will help us investigate whether there is a relationship between behaviour change, discounting, and financial incentives. Briefly, the behavioural economic field experiment will be conducted in maximum groups of 20 participants during lunchtimes. Participants will be offered a £20 gift voucher for taking part in the behavioural economic field experiment. Participants will face several dichotomous decision tasks, such as a risk preference choice task and a monetary discount rate choice task. After the choice tasks, the participant will randomly select the choice occasion and the alternative that will count for payment, and will throw a 10-sided die to determine whether the final payment will take place.

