### Update on study progress

During the recruitment phase for the study, a revised power calculation was undertaken assuming a less demanding effect size estimate taken from the recent literature together with our actual baseline data on mean and variance of cluster size and an intra-class correlation co-efficient of 0.029. In the original protocol, the sample size calculation for the trial was determined using an anticipated effect size of d = 0.21 (based upon a previous meta-analysis of workplace based physical activity interventions). However none of the included studies were incentive-based interventions for physical activity. More recent literature has been published [99, 100], including a meta-analysis in which a mean effect size for incentive based interventions of 16 min of MVPA per day was estimated, equating to an effect size of approximately 1600 steps (d = 0.40). Additionally, in the TRIPPA study [100], which is examining the influence of financial incentives on the effectiveness of a wireless-upload pedometer to encourage weekly physical activity goals, the study was powered to detect a difference of a minimum of 30 min of MVPA per week between groups and power calculations were based on considerably higher effect size than assumed in our original protocol (0.35). Therefore, under the assumption that our original estimate was too conservative, the power calculation has been updated. For an effect size of 0.40, a study of 330 per group (or 660 in total) would have 90 % power at the 5 % significance level. Assuming a 15 % drop-out, the study would need to randomise 776 participants.

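### The only stated tool for comparing subgroups' cost-effectiveness is one acceptability curve per subgroup, which gives no uncertainty for the difference between subgroups

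*Protocol article*

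**What the plan says.** Under Economic analyses, uncertainty in the main comparison is handled by resampling: "The uncertainty surrounding the estimates of cost and effects for the Intervention and Control Group will be investigated through the use of bootstrapping". The next sentence turns to subgroups. It presents the comparison as a sensitivity analysis ("In a sensitivity analysis we will compare subgroups") and gives the method as plotting each subgroup's acceptability curve: "compare subgroups and assess the uncertainty in their incremental cost-effectiveness ratios (ICERs) by plotting the associated cost-effectiveness acceptability curves". Neither that section nor the employer-perspective text after it names a between-subgroup contrast in costs, QALYs or net benefit.

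The Statistical analysis section treats the same kind of question differently for steps per day: "The model will then be extended through the inclusion of interactions involving group and relevant covariates to test for any differential effects". It adds a caution because of multiple testing: "these subgroup analyses will be cautiously reported as hypothesis generating rather than confirmatory". It then repeats these analyses for the health, wellbeing and work outcomes. Neither the interaction nor the caution is carried over to the economic comparison.

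**The concern.** An acceptability curve at a given willingness to pay is the probability that one subgroup's net benefit is positive. Two features make a pair of curves a poor way to compare subgroups. First, height depends on the standard error as well as on net benefit, so a less precise subgroup sits closer to 0.50 at the same true value. Second, no property of the two curves shows how uncertain their difference is. A reader who sees one curve well above the other has no means of telling a real difference from chance.

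Calling the exercise a sensitivity analysis makes this worse. Comparing subgroups does not vary an assumption of the base case. It is a subgroup analysis, and under the other name it escapes the caution that the protocol applies to its other subgroup work. At stake is any statement about the groups for whom the scheme is worth its cost.

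**Working it through.** **Inputs from the article (Update on study progress).** Effect size 0.40, 330 per group, 90% power, 5% significance, 15% drop-out, intra-class correlation 0.029.

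**Assumptions.** The article gives no net-benefit figure and no subgroup sizes. I assume an overall net-benefit z (net benefit divided by its SE in the whole sample) of 0 to 3, splits of 25/75 and 50/50, and the steps ICC for net benefit. The 0.20 gap and the 0.80 level are illustrative and are not in the article.

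**1. The plan's own figure.** 660/0.85 = 776.5, which agrees with the stated 776 to within rounding. The article states no figure for the subgroup curves.

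**2. Implied clustering.** Without clustering, n per group = 2(1.960 + 1.282)²/0.40² = 131.3. The design effect is 330/131.3 = 2.5125, and the effective cluster size is 1 + 1.5125/0.029 = 53.2. The mean and variance of cluster size are not given, so this step is inferred.

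**3. Subgroup SE, with the whole-sample SE set to 1,** for a subgroup of fraction f:
- Independent data: 1/√f. This gives 2.00 and 1.155 at 25/75, and 1.414 each at 50/50.
- Clustered, with subgroups cutting across clusters: √{[1 + (53.2f − 1)0.029]/(2.51f)}. This gives 1.47 and 1.06 at 25/75, and 1.18 each at 50/50.

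**4. Effect of size alone.** Curve height at the true value is Phi(z/SE). At z = 2 and 25/75:
- Independent: Phi(2/2.00) = 0.84 v Phi(2/1.155) = 0.96.
- Clustered: Phi(2/1.47) = 0.91 v Phi(2/1.06) = 0.97.

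At 50/50 the two heights are equal. At zero net benefit every height is 0.50 whatever the size.

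**5. Correlation from shared clusters.** The subgroup variances V1 and V2 must combine to the whole-sample variance: f²V1 + (1 − f)²V2 + 2f(1 − f)cov = 1.
- 25/75: 0.0625 × 2.159 + 0.5625 × 1.129 = 0.770; cov = 0.230/0.375 = 0.613; correlation = 0.613/(1.469 × 1.062) = 0.39.
- 50/50: 2 × 0.25 × 1.386 = 0.693; cov = 0.307/0.5 = 0.614; correlation = 0.614/1.386 = 0.44.

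**6. Repeated trials with identical true net benefit.** Pairs of subgroup z-statistics were simulated with the SEs and correlations above, and each was turned into a height by Phi. Ranges run from clustered with shared clusters (low end) to independent (high end).

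| Overall z | Gap ≥ 0.20, 25/75 | Gap ≥ 0.20, 50/50 |
|---|---|---|
| 0 | 52-64% | 50-64% |
| 1 | 44-58% | 40-56% |
| 2 | 26-42% | 20-36% |
| 3 | 10-25% | 5-16% |

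At z = 2 the curves fall on opposite sides of 0.80 in 29-46% of trials (25/75) and 24-41% (50/50).

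**7. Comparator.** A direct test of the difference in net benefit on the same simulated data rejects in 5% of trials in every case.

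**The case against.** The strongest reply is grammatical. Plotting may attach only to assessing the uncertainty in each subgroup's ICER, which is the ordinary and valid use of an acceptability curve. On that reading the formal contrast is a detail that a condensed article leaves to a fuller plan. This has weight, but the reading in which plotting is the means of comparison is equally natural, and the sentence offers no other means.

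Several stronger claims are tempting and are not supported:

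- *The plan will declare one subgroup cost-effective and another not.* A reader might infer this, but the article sets no gap, cut-off or decision rule.
- *Subgroup size drives the divergence.* Step 4 shows a modest effect at 25/75 and none at 50/50 or at zero net benefit. The 50/50 column shows that sampling noise alone produces most of the gaps.
- *The rates are higher once clustering is allowed for.* Treating subgroups that share clusters as independent would put the clustered z = 2 figures at 32% and 36% (25/75) and 27% and 31% (50/50) for the gap and the opposite-sides result. Shared cluster effects bring them down to 26% and 29%, and 20% and 24%.
- *The inequalities aim rests on these curves.* The RE-AIM section ties that aim to physical activity participation, for which the interaction tests and the caution already apply.

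It is also fair that economic evaluation is often framed as estimation or decision rather than testing, so the 5% benchmark is partly a preference. That does not remove the need for an interval around the difference.

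**Conclusion.** The point holds as a minor one. The method named for comparing subgroups' cost-effectiveness does not estimate the difference between them or its uncertainty, although the protocol uses a suitable contrast for its other outcomes. Truly identical subgroups would often show visibly different curves unless overall net benefit were strongly positive: at an assumed z of 2 about one trial in five to two in five shows a gap of 0.20 or more, and at z of 3 and a 50/50 split the rate can be as low as 5%. These figures rest on a normal approximation to the bootstrap, the assumed z and splits, and the steps ICC applied to net benefit. The primary outcome, the sample size and the main economic result are unaffected.

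**What to change.** Add an arm-by-subgroup interaction on net monetary benefit, keeping the cluster random intercept and the organisation terms of the primary model. Report the difference in incremental net benefit between subgroups with a 95% CI at stated willingness-to-pay values. Keep the subgroup acceptability curves as display only. Call the exercise a subgroup analysis and extend to it the hypothesis-generating label in the Statistical analysis section.

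The cost is a few lines of wording and one extra regression per subgroup variable, with no new data. The downsides are that willingness-to-pay values must be stated and that the intervals will be wide.
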